#### Quality control and feasibility

Feasibility will be monitored by recording numbers of potential participants who are recruited into the study, the number of sessions undertaken out of the possible number of sessions available during the inpatient stay, and reasons for missed sessions.

Assessment of post-study outcome measures will be performed by a neurological physiotherapist who is not involved in the provision of therapy to that client. This will ensure blinding of assessment and maintain the quality of this project. It is not possible to blind the participant as to the group allocation.

#### Efficacy

##### Physical activity

All participants will have their activity monitored for 1 week during the trial by using an accelerometer (ActivPal; PAL Technologies, Glasgow, UK). These devices have been validated in older people with impaired function [18]. Data will be analysed in each group to determine the amount of time spent in activities of low, moderate and high energy expenditure. Energy expenditure during rehabilitation will also be compared between groups.

##### Upper-limb function

Upper-limb function will be measured by using the Upper Arm Function component of the Modified Motor Assessment Scale. This test uses a six-point scale to measure a progression of proximal arm strength and has been shown to be reliable in this population [12]. The box and block test will also be used to provide quantitative results [8].

##### Sitting balance

Sitting balance will be measured by using the standardised sitting balance test, which uses a four-point rating scale to measure sitting balance from poor to normal. It correlates significantly with other measures of function [17].

##### Standing balance

Standing balance in the anterior-posterior direction will be measured by using the Functional Reach test [9], and balance control in the medio-lateral by using the Lateral Reach test [4]. Functional Reach measures dynamic balance control during a self-generated perturbation anteriorly. Participants will stand next to a wall and use their less-affected arm to measure reach distance. Lateral reach measures side-to-side reach ability and will be measured with the participant in an upright position and reaching to the side. The shoulder landmark will be used for each side to ensure that shoulder range does not limit the test. This test can be performed in a seated position if the therapist deems this necessary for safety.

##### Dynamic balance

Dynamic balance will be assessed by using the step test, which involves tapping the foot on and off a step within a 15-second time frame and recording the number of repetitions [11].

##### Mobility

Mobility will be measured by using a 10-meter walk test. Participants will be asked to walk 10 meters using their usual gait aid, and measurements of time taken, stride length, cadence and rate will be recorded [7]. Functional mobility will also be recorded by using the “timed up and go” test [15].

#### Safety

Adverse events during both intervention care and usual care will be recorded. Also, after each session, participants will provide the following data of their experience participating in the group or using the technology: Borg rating of perceived exertion scaleVisual Analogue Scale (VAS) (pain)VAS (fatigue)5-point Likert Scale (enjoyment)5-point Likert Scale (perceived benefit).

Therapists involved in the delivery of the JRS WAVE will be invited to complete an anonymous survey that asks for their feedback on the utility of the system. Perspectives on potential benefits and harm will also be recorded.

### Data Collection

Flow through the study is identified in Fig. 1.

**Fig. 1 Fig1:**
[figure not shown]
Feasibility Interactive Digital (FIND) technology protocol flow diagram

### Data analysis

Data collected during the trial will allow us to describe the participants’ changes in upper-limb function, balance and mobility by using *t* tests or Mann–Whitney *U* tests to compare normally and non-normally distributed data, respectively. Repeated measures analysis of variance will be used to compare changes in the outcome measures over time and between groups (intervention versus control). The level of significance will be set at 0.05.

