#### Sample size and justification

Sample size calculation was based on previously reported clinical trial data and based on the outcome measure of functional reach, that provided baseline mean (standard deviation) data of 25.6 (7.4) cm [14]. Researchers determined that a clinically relevant difference of 3.7 cm would require a sample size of 63 (*P* <0.05, power 80 %). Seventy-four participants will be recruited to allow for a 15 % dropout rate. The proposed size of this study is comparable to more recently published trial data, which suggest that a clinical difference of 3 cm would require 78 participants [3].

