#### Study design

All participants will undergo two measurement sessions by a physiotherapist blinded to group allocation: one on entry into the study (pre-test) and one after the 8-week period (post-test) or prior to discharge if discharged before 8 weeks. All pre-test measures will be completed prior to randomization.

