#### Randomization

Allocation into intervention or control group will be performed by using a computer-generated random number schedule with variable block sizes 2–6. Generation of the randomization sequence will be generated by a researcher not involved in recruitment or assessment. Group allocation will be concealed by using consecutively numbered opaque sealed envelopes, opened in the presence of the participant after completion of assessment.

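### For the continuous physical measures, ANCOVA on the post-test would generally be more efficient than the planned change-score t test and repeated-measures ANOVA, at no cost

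*Protocol article*

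**What the plan says.** Under Study design, the protocol article sets two blinded measurement sessions, one on entry and one at 8 weeks or before an earlier discharge. It states that "All pre-test measures will be completed prior to randomization".

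Under Data analysis, the first sentence describes "changes in upper-limb function, balance and mobility by using" t tests or Mann–Whitney U tests, according to the distribution of the data. The next sentence reads "Repeated measures analysis of variance will be used to compare changes in the outcome measures over time and between groups". No baseline covariate is named, and "The level of significance will be set at 0.05".

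The sample size rests on functional reach. An earlier trial "provided baseline mean (standard deviation) data of 25.6 (7.4) cm", and the section concludes that "a clinically relevant difference of 3.7 cm would require a sample size of 63". It then says "Seventy-four participants will be recruited to allow for a 15 % dropout rate".

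The primary efficacy outcome, according to the Discussion, is activity level. The Physical activity section has it monitored by accelerometer for one week during the trial and describes no baseline recording.

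**The concern.** In a two-arm trial with one measurement before randomisation and one after, the post-test can be compared with adjustment for the pre-test. A change score fixes the coefficient of the pre-test at 1, whereas ANCOVA estimates it from the data. When the pre-post correlation is only moderate, a coefficient of 1 over-corrects and adds noise. Below r = 0.5 (equal SDs) the change score is less precise than ignoring the baseline altogether. Because the repeated-measures ANOVA leads to the same group-by-time test, naming it next to the t test brings no extra information.

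At stake is precision on reach, hand function, stepping, walking and timed up and go, in a trial whose evaluable number is small for its stated target difference. The Discussion itself expects that participants' differing disability will make between-group differences hard to determine. Adjustment for each participant's own starting value is the direct answer to that problem.

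**Working it through.** **Inputs**
- SD 7.4 cm, difference 3.7 cm (0.5 SD), 80% power, alpha 0.05: Sample size and justification. Two-sided testing and 1:1 allocation are not stated and are assumed.
- Evaluable number: 74 × 0.85 = 62.9, so 63, or 31.5 per arm on average.
- Two sessions, the pre-test before randomisation: Study design.
- Pre-post correlation r and post-test SD: not in the article. A range of r from 0.3 to 0.9 is assumed, with a post-test SD of 7.4 cm and at first an equal pre-test SD.

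**1. The plan's own figure.** n per arm = 2 × (1.960 + 0.842)² × (7.4/3.7)² = 2 × 7.85 × 4 = 62.8, so 63 *per arm* or 126 in total. The article uses 63 as the total: 63/0.85 = 74.1, hence 74. With 63 in total, an unadjusted post-test comparison has about 50% power (noncentral t).

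**2. Equivalence.** With two time points and two arms, the group-by-time contrast is the difference between arms in mean (post − pre). Its F statistic is the square of the change-score t statistic. This covers the t-test branch only, not the Mann–Whitney branch.

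**3. Variances per participant (equal SDs).** Change score: 2σ²(1 − r). ANCOVA: σ²(1 − r²). Ratio: (1 − r²)/[2(1 − r)] = (1 + r)/2.

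**4. Power.** The noncentrality is 3.7/[SD × √(2/31.5)], with 61 df for the change score and 60 for ANCOVA. At r = 0.5 the change SD is 7.4 × √1 = 7.40 cm and the ANCOVA SD is 7.4 × √0.75 = 6.41 cm. The noncentralities are 1.98 and 2.29.

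| r | Change SD (cm) | ANCOVA SD (cm) | Variance ratio | Power, change | Power, ANCOVA |
|---|---|---|---|---|---|
| 0.3 | 8.76 | 7.06 | 0.65 | 38% | 54% |
| 0.5 | 7.40 | 6.41 | 0.75 | 50% | 62% |
| 0.6 | 6.62 | 5.92 | 0.80 | 59% | 69% |
| 0.7 | 5.73 | 5.28 | 0.85 | 71% | 78% |
| 0.8 | 4.68 | 4.44 | 0.90 | 87% | 90% |
| 0.9 | 3.31 | 3.23 | 0.95 | 99.2% | 99.4% |

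A simulation with 31 per arm and 4,000 trials per r agreed: 38% vs 54% at r = 0.3, 49% vs 60% at 0.5, 72% vs 78% at 0.7 and 86% vs 89% at 0.8. Both estimators averaged 0.50 to 0.51 SD for a true 0.50. Within a single trial the two estimates differed with an SD of about 1.3 cm at r = 0.3, 0.95 cm at 0.5 and 0.4 cm at 0.8.

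**5. Unequal SDs.** Let k be the pre-test SD divided by the post-test SD. The change-score variance is σ²(1 + k² − 2rk), where σ is the post-test SD. It exceeds the ANCOVA variance by σ²(k − r)², so the gain is zero when k = r. At r = 0.7, change versus ANCOVA power is 78% vs 78% at k = 0.7, 77% vs 78% at k = 0.8, 71% vs 78% at k = 1 and 58% vs 78% at k = 1.25.

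**6. Does ANCOVA rescue the sample size?** By the normal approximation, 80% power at 31.5 per arm needs 1 − r² ≤ 31.5/62.79 = 0.502, so r of at least about 0.71. Below that it does not.

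**The case against.** The strongest defence is that nothing in the planned analysis is invalid. Under randomisation, change-score t tests and the group-by-time test are unbiased and keep their type I error. They also use the baseline, with a fixed slope of 1, so a reader who infers that the pre-test is thrown away would be wrong. This stands, and it makes the point one of efficiency.

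The size of the gain is also open. The article gives neither r nor a post-test SD. At r = 0.8 the gain is about 3 points, at 0.9 it is negligible, and with unequal SDs it can disappear. This stands too, and is why a range is shown.

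One might add that covariates are commonly left to an analysis plan that is not at hand. That carries less weight here, because the article does name its between-group methods, and those are what is being assessed.

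Two harsher readings are not supported. One is that the methods listed do not suit the four-point sitting balance and six-point arm scales. Mann–Whitney is a standard test for ordinal data, and it is not the same test as the ANOVA. The other is that efficacy would be judged on the ANOVA group main effect, which averages in the baseline. The sentence speaks of comparing changes over time and between groups, which most naturally means the interaction.

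**Conclusion.** The point holds as a free improvement for the continuous physical measures. The planned test is valid, but ANCOVA targets the same between-group effect with a large-sample variance that is never larger; the cost is one degree of freedom. With equal SDs, 63 evaluable and a 0.5 SD effect, the gain is about 16 points of power at r = 0.3, 12 at 0.5, 7 at 0.7 and 3 at 0.8. These figures rest on assumed correlations, equal SDs, two-sided testing and 1:1 allocation.

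Two limits apply. ANCOVA does not cure the sample size, where a per-arm number serves as the total; that is a separate matter. Nor do the gains reach the primary activity outcome. With one monitored week and no described baseline, activity needs a direct between-group comparison. A reader might infer that the article plans a change analysis for it, but the text does not clearly say so. The t-test sentence names only upper-limb function, balance and mobility, the ANOVA sentence is merely ambiguous about which outcomes it covers, and the Physical activity section separately announces a between-group comparison of energy expenditure.

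**What to change.** In Data analysis, replace the change-score t test and repeated-measures ANOVA for the continuous physical outcomes (functional reach, lateral reach, box and block, step test, 10-metre walk, timed up and go). Suggested wording: *For each continuous physical outcome, the between-group difference at post-test will be estimated by ANCOVA with arm and the pre-randomisation value of that outcome as covariates, optionally with ward, and reported with a 95% confidence interval.*

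Mann–Whitney can remain for the ordinal scales. State separately that activity will be compared directly between arms, without a change analysis.

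The cost is analysis wording only. The pre-test values and ward are already available, no extra visit or participant is needed, and the article reports recruitment as still under way, so the change can be made before the data are analysed.

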Despite the promise of such low-cost, consumer-based technologies, many, if not all, off-the-shelf video-game solutions are inappropriate for individuals with functional impairment [16]. There is an opportunity for purpose-built, clinically relevant video game-based rehabilitation to add significant value to current rehabilitation practice. Jintronix, a Montreal-based company, has recently launched a Kinect-based rehabilitation system, Jintronix Rehabilitation System (JRS), which provides an easy-to-use software solution (JRS WAVE) for patients to use. The software solution has been designed in collaboration with physical and occupational therapists and draws upon the motor relearning recommendations by Carr and Shepard [5]. As such, upper limb, sitting balance, standing balance and stepping rehabilitation tasks have been programmed in the JRS WAVE as fun and engaging video games that can be played at a number of different levels of complexity and speed. The system is also capable of automatically measuring changes in the range, speed and quality of motion to give patients instant feedback on their progress.

A second feature of the JRS WAVE is a cloud-based client management telehealth system for clinicians to recommend rehabilitation tasks and track and record performance of those tasks (JRS PORTAL). The PORTAL allows clinicians to provide patients regular updates and information on what has happened to them with daily, weekly or monthly progress reports on their rehabilitation, either face-to-face or remotely.

The proposed project will evaluate the feasibility, efficacy and safety of the JRS WAVE for use in an Australian stroke inpatient rehabilitation context. Elements of feasibility include recruitment into the trial, ongoing participation (adherence and dropout), perceived benefit, and enjoyment and ease of use of the games. Efficacy will be determined by measuring physical activity (using an accelerometer) and using upper-limb tasks as well as measuring changes in balance and mobility over time between the two groups. Adverse events will be monitored and changes in pain and fatigue with the interventions will be used to determine safety of the system. We will test the hypothesis that the intervention group will have increased levels of physical activity within rehabilitation and improved physical outcomes compared with the control group.

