## Discussion

The proposed project will discuss the feasibility and efficacy of the JRS WAVE. Uptake from screening to recruitment, adherence to the intervention and rates of dropout will be discussed. Feedback from clinicians in terms of system utility will be explored. Feedback from clients on the perceived benefits of this type of rehabilitation and enjoyment and ease of use of the games will also be discussed. Changes in pain and fatigue within each session and between the intervention and control groups will be analysed. Differences in activity levels during the two different interventions (JRS WAVE versus group exercise) will be investigated. Between-group differences for outcome measures of upper-limb function as well as balance and mobility will be investigated.

The primary outcome of efficacy consists of the differences in activity levels from using video technology in rehabilitation compared with usual rehabilitation. It will also provide data for new controller- and device-free motion capture software on measures of upper-limb function, balance and mobility. Much of the published research reviewing the effectiveness of interactive technology games with commercial devices has not used motion capture software in a controller-free situation. For example, the wii™ system for balance requires standing on a platform and the upper-limb tasks require the client to hold (or have strapped to their hand if they do not have grasp capacity) a device that the sensor recognises [6].

This software has been iteratively designed with feedback from the clinicians to form a system that meets the needs of stroke clients in the acute hospital setting as they begin their rehabilitation pathway. This system is vastly configurable, giving the clinicians the ability to tailor the program and modify it in an ongoing way to meet the needs of the clients. The different levels of disability of the clients enrolled will provide challenges when determining between-group differences.

Strengths of this study include that it collects feasibility data from both clients and clinicians. It is a well-powered study with an active control group to allow comparisons across a range of functional measures. Also, both groups are matched for time in rehabilitation (rather than the intervention as additional therapy) and this will allow direct comparison of the groups.

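### For the upper-limb, balance and mobility outcomes, the two-session repeated measures ANOVA is a t test on change: less precise than conditioning on the pre-test, and biased if dropout depends on pre-test level differently by arm

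*Protocol article*

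**What the plan says.** The Data analysis section of the protocol article names t tests or Mann–Whitney tests for participants' changes, and then: "Repeated measures analysis of variance will be used to compare changes in the outcome measures over time and between groups (intervention versus control". Study design sets two sessions. The first is completed before randomization. The second is "one after the 8-week period (post-test) or prior to discharge if discharged before 8 weeks".

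Sample size and justification works with functional reach, using "baseline mean (standard deviation) data of 25.6 (7.4) cm", and states that a "clinically relevant difference of 3.7 cm would require a sample size of 63". It continues: "Seventy-four participants will be recruited to allow for a 15 % dropout rate". That is one overall rate, not split by arm.

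Dropout also appears as something to be measured: "Elements of feasibility include recruitment into the trial, ongoing participation (adherence and dropout), perceived benefit, and enjoyment and ease of use of the games". The primary efficacy outcome is a different quantity. The Discussion says "The primary outcome of efficacy consists of the differences in activity levels from using video technology in rehabilitation compared with usual rehabilitation", and the Physical activity section says "All participants will have their activity monitored for 1 week during the trial by using an accelerometer", so it is not a pre-to-post measure.

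**The concern.** The article fixes a particular test for the functional outcomes, and that test makes poor use of the pre-test. With two occasions, the group-by-time term compares mean change between arms. Subtracting the whole pre-test over-corrects whenever the pre-post correlation is below 1, and this costs precision.

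It also leaves the estimate exposed to regression to the mean. If participants with low pre-tests leave one arm more than the other, the completers of that arm start higher and on average change less, even when the treatment does nothing. Participants cannot be blinded and the arms do different activities, so such a pattern is possible. At stake are the between-arm estimates for reach, balance and mobility, which form part of the stated hypothesis and include the outcome on which the trial is sized.

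**Working it through.** **Inputs from the article.** SD 7.4 cm, target difference 3.7 cm, 74 recruited, 15% dropout, two sessions.

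**Assumptions.** 37 per arm; equal SD at both sessions; pre-post correlation r of 0.4, 0.6 or 0.8; no true effect; and the dropout patterns below. The article gives none of these.

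**The article's own figures.** 2 × (7.4 × (1.96 + 0.84) / 3.7)² is about 62.8, so 63, and 63 / 0.85 = 74.1, so 74. This formula gives 63 per arm, which is a separate matter and is not used here. In reverse, 74 × 0.85 = 62.9, so the allowance amounts to about 11 participants.

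**Precision.** The variance of a change is 2σ²(1 − r). The residual variance after regression on the pre-test is σ²(1 − r²). The ratio of standard errors, conditional to change, is √((1 + r)/2):
- r = 0.4: √0.70 = 0.837, 16% smaller
- r = 0.6: √0.80 = 0.894, 11% smaller
- r = 0.8: √0.90 = 0.949, 5% smaller

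Estimating the slope in a small trial takes back about a percentage point, and simulation with random dropout puts the lower end at 3% to 4%. Taken the other way, by the formula, the change analysis has a standard error 5% to 20% larger. In patients, the total needed for 3.7 cm at r = 0.6 is 102 with a change analysis and 82 with a conditional one.

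**Bias when dropout depends on the pre-test.** Let Δ be the amount by which the mean pre-test of an arm's completers exceeds that of everyone randomised to it. Their mean post-test is raised by rΔ, so their mean change is shifted by −(1 − r)Δ. The bias is the difference between arms in this shift. Suppose control loses 10% at random and the technology arm loses 20%, with the odds of leaving multiplied by e (slope 1) or e² (slope 2) per SD of lower pre-test. Numerical integration gives Δ = 0.173 SD = 1.28 cm (slope 1) or 0.262 SD = 1.94 cm (slope 2).

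| r | slope 1: −(1 − r) × 1.28 | slope 2: −(1 − r) × 1.94 |
|---|---|---|
| 0.4 | −0.77 cm | −1.16 cm |
| 0.6 | −0.51 cm | −0.78 cm |
| 0.8 | −0.26 cm | −0.39 cm |

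Simulation of 5,000 trials per setting agrees: −0.75, −0.56 and −0.24 cm at slope 1, and −1.13, −0.74 and −0.41 cm at slope 2. The rejection rate under no effect was 5.4% to 6.6% at slope 1 and 6.2% to 8.4% at slope 2. Regression of post-test on pre-test and arm stayed within 0.05 cm of zero, with rejection of 4.7% to 5.3%.

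**Other dropout patterns** (bias of the change comparison at slope 1, r = 0.4, 0.6, 0.8):
- 15% in both arms, same slope: within 0.05 cm of zero.
- 20% technology against 10% control, same slope in both: −0.37, −0.25, −0.10 cm.
- 15% in both arms, selective in the technology arm only: −0.56, −0.42, −0.20 cm. Equal dropout counts alone do not remove the bias.

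**Dropout that follows the unseen post-test.** With the same 20% against 10% and slope 1, completers' post-tests shift by 1.28 cm and their pre-tests by r × 1.28. The change comparison is then biased by (1 − r) × 1.28 = +0.77, +0.51 and +0.26 cm. The conditional one is biased by about (1 − r²) × 1.28 = +1.08, +0.82 and +0.46 cm, so here it is the worse of the two.

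**Which feature causes the pre-test-related bias.** The regression that removes it is also fitted only to participants with a post-test. With every pre-test observed and only post-tests missing, a two-occasion likelihood model with a common pre-test mean gives the same arm estimate. Participants without a post-test inform the pre-test mean, not the arm effect. The fault is therefore the failure to condition on the pre-test, not the loss of about 11 people.

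**The case against.** The strongest reply is that this criticises silence. The article states no analysis set and no missing-data rule, and both may sit in a full protocol or analysis plan that is not shown. That stands: their absence is no finding, and naming a repeated measures ANOVA does not rule out imputation. The point rests only on the test that the article does name, and the precision loss needs no dropout at all.

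Second, the size of the bias comes from chosen scenarios. This also stands. The sign, the size and even which method does better depend on why people leave, and at the milder slope the type I error is at most 6.6%.

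Third, Study design already provides a post-test for all participants, brought forward for those discharged early, and does not make it conditional on continuing the sessions. That reduces missing data, although the sample size still allows for 15%.

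A reader might go further and infer that efficacy will be tested in 63 completers, or that the article expects the technology to cause dropout. It says neither. The 63 is a required number, and dropout is a feasibility measure to be recorded and discussed, with no arm difference predicted.

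**Conclusion.** The point holds as a modest, conditional one. The loss of precision follows from the named test: the standard error of a conditional analysis is about 3% to 16% smaller for correlations of 0.8 to 0.4. The bias is a risk, not a certainty. It runs from near zero, when dropout is alike in both arms, to about −0.25 to −0.8 cm at the milder assumed slope, which is 7% to 21% of the 3.7 cm target (0.26/3.7 and 0.77/3.7). At the steeper slope it reaches about −1.2 cm. The correlations, slopes and arm split are all assumptions.

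The conclusion covers the upper-limb, balance and mobility outcomes, with the figures worked for functional reach. It would be wrong to extend it to all efficacy tests, because the primary activity outcome comes from a single monitored week and has no pre-to-post change.

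**What to change.** For the continuous functional outcomes, replace the repeated measures ANOVA with a model of participants in the arm to which they were randomised that conditions on the pre-test. This can be a two-occasion likelihood model with a common pre-test mean and the arm effect at post-test only, or equivalently a regression of post-test on pre-test and arm.

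Neither form protects against dropout driven by the post-test value that was not seen. Add one sensitivity analysis that shifts the missing post-tests, by arm, until the conclusion changes, and report the shift needed.

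The cost is a paragraph of analysis wording and slightly more analysis work. No extra patients or sessions are needed, because the pre-tests are already collected before randomization.

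### The continuous and count physical outcomes are compared on unadjusted pre-to-post change; adjusting the post-test for the pre-test already collected would generally be more precise

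*Protocol article*

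**What the plan says.** The Data analysis section of the protocol article names two approaches for the physical outcomes. First, it will "describe the participants’ changes in upper-limb function, balance and mobility by using" t tests for normally distributed data or Mann–Whitney U tests otherwise. Second, "Repeated measures analysis of variance will be used to compare changes in the outcome measures over time and between groups (intervention versus control"). Neither sentence names a baseline covariate, and no other section does.

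Under Study design, "All participants will undergo two measurement sessions by a physiotherapist blinded to group allocation: one on entry into the study (pre-test") and one at eight weeks or before an earlier discharge. The same section states that "All pre-test measures will be completed prior to randomization".

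The sample size is "based on the outcome measure of functional reach", from earlier trial data "that provided baseline mean (standard deviation) data of 25.6 (7.4) cm", with a target difference of 3.7 cm. The Discussion expects that "The different levels of disability of the clients enrolled will provide challenges when determining between-group differences".

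**The concern.** Each physical outcome has exactly one value before randomisation and one after. The pre-test is therefore a legitimate covariate that is already collected. The plan uses it only by subtracting it, which fixes the baseline slope at 1 whatever the data show. A model that estimates the slope is, in large samples, at least as precise, and its estimate does not move with a chance baseline difference between arms.

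At stake is precision on the continuous and count measures: functional and lateral reach, box and block, step test, gait measures, and timed up and go. These carry the part of the hypothesis about improved physical outcomes, and functional reach is the measure used to size the trial. With about 31 or 32 analysed per arm, a chance baseline difference of practical size is likely enough to matter.

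**Working it through.** **Inputs.** From Sample size and justification: SD 7.4 cm (a baseline SD), difference 3.7 cm, 63 analysed. From Data analysis: significance level 0.05. Assumed because not stated: two-sided testing, 1:1 allocation (32/31), the pre-post correlation r, and a post-test SD equal to the pre-test SD.

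**The plan's own figure.** For a two-sample comparison of a single measurement, n per arm = 2 × (1.960 + 0.842)² × (7.4/3.7)² = 62.8, so 63 per arm. The protocol uses 63 as the total (63/0.85 = 74.1, hence 74 recruited). That is a separate issue, but it explains why the absolute power levels below are low: 63 in total gives about 50% power on the post-test alone.

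**Equivalence.** With two occasions, the group-by-time F statistic in a repeated measures ANOVA is the square of the t statistic comparing mean change between arms. The t test and the ANOVA interaction are therefore one unadjusted analysis.

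**Precision with equal SDs.**
- Change: SD = 7.4 × √(2(1 − r))
- Post-test adjusted for pre-test: SD = 7.4 × √(1 − r²)
- Ratio of variances, adjusted to change: (1 + r)/2, a reduction of (1 − r)/2

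Power is by the noncentral t distribution, 32/31 analysed, two-sided 5%:

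| r | SD change (cm) | SD adjusted (cm) | Power, change | Power, adjusted | Variance reduction |
|---|---|---|---|---|---|
| 0.3 | 8.76 | 7.06 | 38% | 53% | 35% |
| 0.5 | 7.40 | 6.41 | 50% | 62% | 25% |
| 0.7 | 5.73 | 5.28 | 71% | 78% | 15% |
| 0.8 | 4.68 | 4.44 | 87% | 90% | 10% |
| 0.9 | 3.31 | 3.23 | 99.2% | 99.4% | 5% |

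At r = 0.5 the change score has the same SD as the post-test alone. Below that it is less precise than ignoring the pre-test.

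**Precision with unequal SDs.** Let k = post-test SD / pre-test SD. In units of the pre-test variance, change has variance 1 + k² − 2rk and the adjusted analysis k²(1 − r²). The best baseline slope is rk.
- r = 0.8, k = 1.25: slope 1.00; variances 0.5625 and 0.5625; no gain.
- r = 0.7, k = 1.3: slope 0.91; variances 0.870 and 0.862; gain about 1%.
- r = 0.5, k = 1.3: slope 0.65; variances 1.390 and 1.268; gain about 9%.

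**Chance imbalance.** The standard error of the baseline difference is 7.4 × √(1/32 + 1/31) = 1.86 cm. Given an observed imbalance, the change estimate shifts by (rk − 1) × imbalance. With k = 1 and r = 0.5, one standard error of imbalance shifts it by 0.5 × 1.86 = 0.93 cm in the opposite direction, a quarter of 3.7 cm. A simulation with 32/31 per arm and equal SDs gave slopes of the estimate on the imbalance of −0.49 (r = 0.5) and −0.30 (r = 0.7) for change, and about 0 for the adjusted model.

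**The case against.** The strongest reply is that the planned comparison is valid: over randomisation, both change and adjusted post-test estimate the treatment effect without bias. The imbalance shift exists only conditionally on the difference that happens to occur. This stands, so the point is one of efficiency and not of a wrong analysis.

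The size also rests on two quantities that the document does not give. If r is 0.8 to 0.9, or the post-test spread is larger than the pre-test spread, little or nothing is gained. The Discussion's remark on differing disability can cut this way too, because stable differences between patients raise r and change scores already remove much of them. A reader might infer that change is less efficient whenever r is below 1 and always over-corrects baseline differences. The unequal-SD cases show that neither holds in general.

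A reader might also take the ANOVA's group main effect as the treatment test. That averages in the pre-test and estimates half the effect. The text speaks of comparing changes between groups, which is the interaction, and nowhere proposes the main effect, so this reading is not supported.

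That an analysis plan may settle covariates elsewhere does not dispose of the point, since the article states its between-group methods outright. Two further objections do stand and limit the fix. The plan provides a Mann–Whitney option for non-normal data, and any replacement must keep such a provision. And under Standing balance the reach testing may be done seated where needed for safety, so a participant's pre-test and post-test may not always be taken in the same position.

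**Conclusion.** The concern holds as an efficiency point on the continuous and count physical measures. The document fixes an unadjusted change comparison although a pre-randomisation value of each measure is collected, and the baseline-adjusted model is asymptotically at least as precise. With equal SDs the variance reduction runs from 35% at r = 0.3 to 5% at r = 0.9. With a larger post-test SD it is smaller, and zero in the case r = 0.8, k = 1.25.

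Three limits apply. The low absolute power in the table should not be charged to the analysis method: it comes mainly from the sample size figure, and only the gap between the two power columns belongs here. The point does not extend to the ordinal upper-arm and sitting-balance scales. Nor does it reach the primary efficacy outcome: functional reach sizes the trial, but the Discussion names activity level as primary, and the Physical activity section describes one week of monitoring during the trial with no pre-test.

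**What to change.** In Data analysis, for functional and lateral reach, box and block, step test, gait measures, and timed up and go, make the between-group test a linear model of the post-test value on randomised arm with the same measure's pre-test value as covariate. Report the adjusted difference with its 95% confidence interval. Keep change scores as description. Where residuals are clearly non-normal, use a transformation or a rank-based or robust version of the same baseline-adjusted model, so that the present provision for non-normal data is replaced and not lost. Leave the ordinal scales and the activity outcome outside this change.

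The cost is a change of wording and one degree of freedom per model. No new data or participants are needed.
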